### **10.1 Primary study parameter(s)**

Clinically relevant deterioration expressed as the number of patients transferred from a general ward to the ICU and the number of patients who die on the general ward or in the ICU.

### **10.2 Secondary study parameter(s)**

Total number of deaths and total number of days of hospital admission.

### **10.3 Other study parameters**

BSE, CRP, leukocytes, ferritin, oxygen saturation at admission, and temperature progression. These measurements and tests are performed as part of routine care.

#### **10.4 Interim analysis (if applicable)**

Halfway through the study, with 50 inclusions per arm, an interim analysis will be performed. There are two reasons why the study may be stopped early:

1. Due to futility. The study will be stopped if, upon recalculation of the sample size, more than 100 participants per arm are needed or the difference between control and intervention arm is not considered clinically relevant (i.e., less than 5% difference).
2. Due to effectiveness (O'Brien Fleming stopping rule). The study will be stopped at a p-value < 0.0054 for the null hypothesis (i.e., no difference between intervention and reference).

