### **4.4 Sample size calculation**

If a less optimistic scenario is assumed, with 25% deterioration (transfer to ICU or death on ward or in ICU) in the control arm and 10% in the intervention group, the power calculation is as follows: 25% vs 10% → 100 subjects per group → 200 subjects total → 10% dropout → 224 subjects needed. An interim analysis is planned with stopping rule according to O'Brien Fleming, for which no adjustment of the sample size is needed. After 50 patients in each arm

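### The futility limit of 100 per arm equals the planned size, so the trial would stop about half the time when the planned effect is true, and power falls from about 81% to about 49%

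*Protocol*

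**What the plan says.** Protocol section 4.4 bases the size on "with 25% deterioration (transfer to ICU or death on ward or in ICU) in the control arm and 10% in the intervention group" and carries this through as "100 subjects per group → 200 subjects total → 10% dropout → 224 subjects needed". It mentions an O'Brien-Fleming stopping rule, "for which no adjustment of the sample size is needed".

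Section 10.4 sets the timing: "Halfway through the study, with 50 inclusions per arm, an interim analysis will be performed". It gives two futility conditions, either of which is enough. The first is "The study will be stopped if, upon recalculation of the sample size, more than 100 participants per arm are needed". The second is that "the difference between control and intervention arm is not considered clinically relevant (i.e., less than 5% difference" applies. The efficacy stop is at p < 0.0054. The protocol names no method for the recalculation, does not call the futility rule non-binding, and gives no power with the rule in force. Section 9.5 marks a data safety monitoring board as not applicable.

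**The concern.** A futility rule should stop a trial that is unlikely to succeed. Here the limit on the recalculated size is the same number as the planned size, and the planned size is what the design effect itself requires. An interim estimate a little below 15 points therefore triggers the stop, and with 50 per arm the estimate falls below the true value about half the time.

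At stake is the power of the trial. A treatment with exactly the effect that the trial was sized to detect would be abandoned as futile about as often as not. Section 4.4 does not show this, because its size takes no account of the futility rule.

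**Working it through.** **Inputs.** From section 4.4: 25% versus 10%, 100 per arm, 10% dropout. From section 10.4: interim at 50 per arm, futility limit of 100 per arm, 5-point limb, efficacy stop at p < 0.0054. Assumed: two-sided alpha 0.05 and 80% power, which the protocol does not state.

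**1. The plan's own figure.** Two-proportion formula with pooled variance under the null, where p̄ = 0.175 and d = 0.15:

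n = [1.96·√(2p̄(1−p̄)) + 0.84·√(p₁(1−p₁) + p₂(1−p₂))]² / d² = 99.5, so 100 per arm.

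Other choices do not fit: 113 with continuity correction, 133 at 90% power, 79 one-sided. Dropout: 100/0.9 = 111.1, so 112 per arm and 224 in total, as stated.

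**2. What the limit means at the interim.** If the size is recalculated from the observed rates, then approximately n = 50·(1.96 + 0.84)²/z², where z is the interim test statistic. Requiring n ≤ 100 gives z ≥ 2.80·√(50/100) = 1.98, or p of about 0.048 or less.

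**3. Recalculated size for some observed rates (same formula).**

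| Control vs intervention | Difference (points) | n per arm | Result |
|---|---|---|---|
| 25% vs 10% | 15 | 99.5 | continue |
| 25% vs 11% | 14 | 117 | stop |
| 25% vs 12% | 13 | 139 | stop |
| 24% vs 10% (12/50 vs 5/50) | 14 | 112 | stop |
| 20% vs 6% | 14 | 89 | continue |
| 16% vs 4% | 12 | 97 | continue |
| 30% vs 14% | 16 | 104 | stop |
| 5% vs 0% | 5 | 152 | stop |

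On this method the 5-point limb almost never decides the outcome. Even 5% versus 0% needs more than 100 per arm.

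**4. Operating characteristics.** All 51 × 51 interim tables were enumerated with exact binomial probabilities. The remaining 50 per arm were then added, with a final pooled z-test at 0.0492. Final levels from 0.048 to 0.05 give the same power to within 0.1 point.

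| True rates 25% vs 10% | Futility stop | Efficacy stop | Power |
|---|---|---|---|
| Efficacy boundary only | none | 20.2% | 81.3% |
| Section 10.4 as written | 49.2% | 20.2% | 49.0% |
| 5-point limb only | 8.9% | 20.2% | 78.6% |

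As written, 100 − 49.2 − 20.2 = 30.6% of trials continue. A normal approximation agrees: 50% stops, and power of 48% against 80%. At a true 25% versus 15%, the written rule stops 76.5% for futility and power is 19.6%, against 42.4% without the futility rule. With no effect (25% in both arms), futility stops are 97% as written and 72% with the 5-point limb alone.

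**5. Sensitivity to the recalculation method (true 25% vs 10%).**

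| Method | Futility stop | Power |
|---|---|---|
| Unpooled variance | 47.0% | 51.0% |
| Continuity correction | 55.4% | 43.5% |
| 90% power | 60.5% | 38.8% |
| 15 points kept, pooled rate updated | 42.4% | 50.8% |
| Planned relative effect kept, control rate updated | 49.0% | 47.5% |
| Final analysis at 112 per arm, limit 100 | 49.2% | 49.5% |

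**The case against.** The strongest defence is that section 10.4 names no recalculation method and opens by saying the study may be stopped, so a statistical analysis plan could soften the rule. That does not rescue it. The protocol itself fixes the threshold, the condition is worded as a mandatory stop, and none of the methods tried brings power above 51%. Reading the limit as 112 per arm, the size after dropout, departs from the text. Even then, with the final analysis at 112 per arm, 43.2% of trials stop and power is 54.9%, against 85.5% with the efficacy boundary alone.

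Several stronger readings are tempting but not supported:

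- A reader might infer that the no-adjustment statement in section 4.4 is false. It refers to the O'Brien-Fleming rule and is fair for that rule alone, since power stays at 81.3%.
- A reader might infer that every benefit of 5 to 14 points stops the trial. The trigger depends on the event rates as well: 20% versus 6% continues, while 30% versus 14% stops. The statement needs a control rate near 25%.
- Section 10.4 says that differences below 5% are not clinically relevant. It does not say that every larger one is.
- A reader might infer that the stopped trials were nearly sure to succeed. Under the planned effect their mean conditional power is (81.3 − 49.0)/49.2, about 66%. About 31% of them have 80% or more, and about 20% have less than 50%. The 12/50 versus 5/50 example, at about 87%, is at the favourable end.
- The 5-point limb is close to redundant only if the size is recalculated from the observed effect. If the 15-point difference is kept and only the event rate updated, it can act.

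**Conclusion.** The point stands and should be corrected before the interim. The futility limit equals the planned size, so the rule as written acts as a demand for nominal significance at half the data. At the planned effect it costs about 32 points of power (81.3% to 49.0%) through a futility stop in about 49% of trials. Near a 25% control rate, observed benefits well above the 5-point limit would stop the trial.

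The exact figures rest on two-sided 5% and 80% power (inferred because they reproduce 100 per arm), recalculation from observed rates, a test of proportions standing in for the log-rank test of section 10, and all 50 outcomes per arm being known at the interim. The alternative recalculation methods give 42% to 60% stops and 39% to 51% power, so the conclusion does not depend on the method chosen. The fault in section 4.4 is that its size ignores the futility rule, not what it says about O'Brien-Fleming.

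**What to change.** In section 10.4, delete the condition on needing more than 100 participants per arm. Keep the plan's own second limb, worded as control minus intervention below 5 percentage points, absolute and in the direction of benefit. In section 4.4, state the power with both interim rules in force: about 79%, with about 9% false futility stops at the planned effect, together with the alpha and power used.

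This takes a short amendment and no patients beyond the planned 224. The downside is that fewer trials stop early when the treatment does nothing: with 25% in both arms, futility stops fall from about 97% to about 72%.

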### **11. ETHICAL CONSIDERATIONS**

#### **11.1 Regulation statement**

The study will be conducted according to the principles of the Declaration of Helsinki (version, date, see for the most recent version: [www.wma.net](http://www.wma.net)) and in accordance with the Medical Research Involving Human Subjects Act (WMO) and other guidelines, regulations, and Acts.

#### **11.2 Recruitment and consent**

Patients will be recruited by nursing staff, physician assistant in training, or attending physician. Consent will be requested by the investigator.

#### **11.3 Objection by minors or incapacitated subjects (if applicable)**

Patients who wish to participate must be 18 years or older and mentally competent.

#### **11.4 Benefits and risks assessment, group relatedness**

The likelihood of side effects is derived from the listings in the pharmacotherapeutic compass for Potassium Iodide 65 mg tablets. The side effects listed there are relatively mild and in principle transient. In rare cases, in patients with pre-existing thyroid disorders, thyrotoxicosis may occur. Temporary medicinal treatment may then be necessary to

correct thyroid dysfunction. However, this is not expected since thyroid disorders or medication related to thyroid dysfunction are exclusion criteria. The risk of side effects at the dosage of Potassium Iodide used in this study is very limited. By applying exclusion criteria for thyroid disorders and medication related to thyroid dysfunction, the chance of thyrotoxicosis is virtually eliminated. Other side effects are relatively minor and usually transient. There are no long-term health risks expected with this short-term Potassium Iodide treatment. The potential benefits for the patient may be significant, such as a better chance of survival, faster recovery, and shorter duration of hospital admission. Furthermore, there may be less irreversible lung damage, so that the quality of life after the illness period will be better.

### **11.5 Compensation for injury**

Subject insurance has been applied for.

### **11.6 Incentives (if applicable)**

Not applicable

## **12. ADMINISTRATIVE ASPECTS, MONITORING AND PUBLICATION**

### **12.1 Handling and storage of data and documents**

Research Manager is used in a secure hospital environment to store data. Source data is stored in a secured Excel file.

### **12.2 Monitoring and Quality Assurance**

Given the short duration of the study, practical arrangements will be made to organize this remotely. Contact has been made with CTCM and an initial visit took place by telephone on April 16.

### **12.3 Amendments**

Amendments are changes made to the research after a favorable opinion by the accredited METC has been given. All amendments will be notified to the METC that gave a favorable opinion. Non-substantial amendments will not be notified to the accredited METC and the competent authority, but will be recorded and filed by the sponsor.

### **12.4 Annual progress report**

The sponsor/investigator will submit a summary of the progress of the trial to the accredited METC once a year. Information will be provided on the date of inclusion of the first subject, numbers of subjects included and numbers of subjects that have completed the trial, serious adverse events/serious adverse reactions, other problems, and amendments.

### **12.5 End of study report**

The investigator/sponsor will notify the accredited METC of the end of the study within a period of 8 weeks. The end of the study is defined as the last patient's last visit. The sponsor will notify the METC immediately of a temporary halt of the study, including the reason for such an action. In case the study is ended prematurely, the sponsor will notify the accredited METC within 15 days, including the reasons for the premature termination.

Within one year after the end of the study, the investigator/sponsor will submit a final study report with the results of the study, including any publications/abstracts of the study, to the accredited METC.

## **12.6 Public disclosure and publication policy**

Not applicable

## **13. STRUCTURED RISK ANALYSIS**

**Risks of ingesting Potassium Iodide are minimal** [10,11,12]. Potassium Iodide tablets of 65 mg are distributed among the population living within a certain distance from a nuclear power plant, with the advice to take a one-time dose of 130 mg in case of a nuclear disaster. The goal is to prevent the uptake of radioactive iodine and thereby prevent thyroid cancer. These tablets are distributed indiscriminately. This is justified because the benefit/risk ratio is high—in other words, the risk of possible mild side effects does not outweigh the risks of developing thyroid cancer.

In the pharmacotherapeutic compass, side effects are described for two indications for Potassium Iodide treatment. In addition to the aforementioned, Potassium Iodide is also given as preparation for thyroid surgery. Dosages used range from 150 to 750 mg per day for 10 to 14 days. The total dosage then amounts to 1,500 mg to 10,500 mg. Even at these dosages, relatively few and mild side effects are described.

Additionally, the website [www.vergiftigingen.info](http://www.vergiftigingen.info) does not advise additional measures for adults who have ingested a one-time dose of  $10 \times 65 \text{ mg} = 650 \text{ mg}$  Potassium Iodide tablets, since no relevant side effects are expected (see appendix 1).

The Potassium Iodide dosage used in our study—16.5 mg per day for 8 days, totaling 130 mg—is safe and the risk of side effects is very limited. The potential benefit of treatment with iodine is substantial, namely a less severe course of COVID-19 disease, a shorter illness period, a greater chance of survival, and possibly less irreversible lung damage.

### 13.1 Potential issues of concern

**The chance of thyrotoxicosis occurring is very small.** Should this nevertheless occur, the symptoms are temporary and transient.

**a. Level of knowledge about mechanism of action** The mechanism of thyrotoxicosis may cause hyperthyroidism due to autonomous dysregulation of the thyroid. It may also temporarily cause hypothyroidism due to blockage of iodine uptake by the thyroid.

**b. Previous exposure of human beings with the test product(s) and/or products with a similar biological mechanism** In previous studies, no relevant side effects were reported at the dosage and administration frequency used in our study [10,11,12].

**c. Can the primary or secondary mechanism be induced in animals and/or in ex-vivo human cell material?** Not known

**d. Selectivity of the mechanism to target tissue in animals and/or human beings** Not known

**e. Analysis of potential effect** Multiple in vitro studies and animal model studies have demonstrated virus inactivation by iodine.

**f. Pharmacokinetic considerations** Iodine is rapidly absorbed into the blood via the intestines. Iodine is actively taken up in the thyroid and is also relatively quickly excreted in various tissues such as mucous membranes.

**g. Study population** All patients aged 18 years and older who are admitted to the hospital and test positive for SARS-CoV-2 infection will be recruited for this study. Patients must be mentally competent and able to read the patient information sheet and sign the informed consent form.

**h. Interaction with other products** Not applicable

**i. Predictability of effect** It is expected that iodine will have a beneficial effect on the course of COVID-19 disease.

**j. Can effects be managed?** Should thyroid dysregulation occur in the very rare case, it is usually temporary and transient. If not, there are medications available to effectively treat this dysregulation.

### 13.2 Synthesis

The chance of medically relevant side effects is very limited at the dosage and administration frequency chosen in our study. Should this unexpectedly occur, the effects are transient or otherwise treatable with medication.

